### Trial design and setting

The Sparky Samba trial is a parallel-group feasibility RCT of the Sparky Samba intervention compared with an activities-as-usual control group. We will recruit 60 PwP to be randomised 1:1 to the intervention or activities as usual for a period of 12 weeks. The recruitment target of 60 has been selected in line with guidance for sample sizes in feasibility studies.^18^ This sample size will allow estimation of recruitment, retention, adherence and data completeness rates with a 95% binomial CI of no more than plus or minus 13 percentage points irrespective of the point estimate. The trial is not powered for hypothesis tests to detect effects in the clinical outcome measures.

The trial will be conducted in three secondary care (National Health Service (NHS)) sites across Wales, UK, with the Sparky Samba intervention delivered at three local community sites identified and supported by the Sparky Samba group. The clinical sites have been selected due to their co-location with the Sparky Samba groups to facilitate attendance of participants at the Samba groups.

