### Randomisation

Participants will be randomised to the intervention or activities as usual in a 1:1 ratio, stratified by disease burden using the Hoehn and Yahr score of disease stage.^21^ The randomisation sequence, generated by the non-blinded, senior trial statistician, using nQuery software and stored securely so those enrolling participants cannot access it, will use permuted blocks of randomly varying sizes. The randomisation will be implemented via REDCap, and allocation to groups will be performed by the central trial team. Allocation will be communicated directly to the participant with concurrent notification to the recruiting site and, if required, the relevant local Sparky Samba group. Randomisation should occur within 14 days of the baseline assessment.

Owing to the nature of the intervention, this is a non-blinded trial. However, the trial statistician will remain blind to allocation until analysis is complete. Further, the Unified Parkinson’s Disease Rating Scale Part III^22^ will be video recorded, and ratings will be performed by a trained clinician blind to the allocation of the participant.

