### Activities as usual

Participants randomised to the activities as usual control group will be asked to continue with their normal activities and attend any social or support groups they would ordinarily participate in over the 12 weeks. Participation in the trial does not necessitate prior or ongoing attendance at a particular social or support group. A physiotherapy or physical activity control group was considered to control for the type of movement included in a Sparky Samba session. However, this was discounted because while there is good evidence that physiotherapy and exercise can benefit PwP,^23
24^ the delivery of physiotherapy and exercise to this patient group, either through healthcare systems or community groups, is inconsistent across the region. Further, in conjunction with our PPI group, we were conscious that the opportunity for social interaction was a key aspect of attending Sparky Samba, which would not be achieved through attendance at healthcare-delivered physiotherapy sessions. The PPI group also suggested that many PwP are involved in other local community groups; therefore, activities as usual was chosen as the control. From the input of the PPI group, we anticipate that activities as usual may consist of activities such as walking, the gym, seated bowls or less physically orientated activities such as a Parkinson’s choir. Given the varied availability of specific Parkinson’s groups or organised community groups, we have not specified activities as usual but will be asking people randomised to this group to specify the activities they have taken part in over the 12-week trial period. This will help us determine the feasibility of using ‘activities as usual’ as a comparator condition in a future effectiveness trial of Sparky Samba. Following completion of the 12-week follow-up assessment, participants randomised to activities as usual will be offered the opportunity to join their local Sparky Samba group. As for trial participants initially randomised to the intervention group, any costs associated with attendance at the Sparky Samba group will be supported by the trial for a period of 12 weeks.

During the intervention delivery period, there are no restrictions imposed on any additional treatment participants may require for their PD or otherwise. If changes in health status and/or treatment affect their participation in the trial, this will be recorded via notification of withdrawal.

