### Outcomes

The primary outcome for this trial is feasibility as defined by participant recruitment, retention, intervention adherence and data completeness according to pre-specified criteria. Thresholds for the feasibility criteria are detailed in table 1.

**Table 1 T1:** Measures of feasibility and pre-defined criteria for success used to determine the primary outcome

Variable	Progression criteria		
	Red	Amber	Green
Recruitment			
% of people approached who are willing to participate (100*(number consented/number approached)%)	<5%	5–19.9%	≥20%
Number recruited	<25	25-44	45-60
Retention			
% of participants attending the primary 12-week endpoint assessment (100*(number attending/number consented)%)	<50%	50–89.9%	≥90%
Adherence			
% of participants adherent to the intervention (attending ≥8 sessions) (100*(number adherent/number consented)%)	<50%	50–79.9%	≥80%
Data completeness			
% of participants completing at least 90% of baseline measures (100*(number completing ≥90%/number consented)%)	<70%	70–94.9%	≥95%
% of participants completing at least 90% of follow-up measures (100*(number completing ≥90%/number consented)%)	<50%	50–74.9%	≥75%

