### Analysis

Key demographic data will be summarised using descriptive statistics. For feasibility outcomes, recruitment will be assessed as the percentage of people approached who provide consent to participate in the trial; retention as the percentage of participants recruited who attend the 12-week follow-up assessment (primary endpoint); adherence as the percentage of participants adherent to the intervention (where intervention adherence is defined as attending ≥8 of 12 sessions) and data completeness as the percentage of participants completing ≥90% of baseline and follow-up measures, respectively (table 1). Feasibility criteria will be assessed according to a traffic light system with green (proceed to full effectiveness RCT) if all criteria listed in table 1 are in the green zone; amber (requiring adjustment before proceeding to full RCT) if all criteria are either in the amber or green zone; and red (do not progress to full RCT unless major changes are implemented) if at least one criterion is in the red zone. For secondary outcome measures, we will calculate descriptive summaries by arm, such as mean and standard deviation (or median and IQR, in case of a distinctly non-normal distribution) and 95% CIs of participants’ changes from baseline to 12-week follow-up. This will provide estimates of effect size and variability of drumming-induced changes for use in power calculations for a future large-scale RCT. No sub-group, sensitivity or interim analyses will be conducted. Reporting of results will follow the Consolidated Standards of Reporting Trials (CONSORT) guideline extension for pilot and feasibility studies.^26^ The statistical analysis plan will be available via ISRCTN (*ISRCTN11861663*).

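### The adherence criterion in Table 1 divides by everyone who consented in both arms, so its ceiling is about 50%: green (≥80%) cannot be reached and red is very likely even with good adherence.

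*Protocol article*

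**What the plan says.** The Outcomes section makes feasibility the primary outcome and sets its criteria in Table 1. The adherence row is the percentage "of participants adherent to the intervention (attending ≥8 sessions) (100*(number adherent/number consented", with red, amber and green bands of "<50% 50–79.9% ≥80" per cent.

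Other parts of the protocol article fix what this means:

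- Trial design and setting: "We will recruit 60 PwP to be randomised 1:1 to the intervention or activities as usual for a period of 12 weeks". The same section names adherence among the rates that 60 participants will estimate to within 13 percentage points.
- Randomisation: "Participants will be randomised to the intervention or activities as usual in a 1:1 ratio", and "Randomisation should occur within 14 days of the baseline assessment". Table 3 places consent before the baseline hospital visit.
- Activities as usual: "Following completion of the 12-week follow-up assessment, participants randomised to activities as usual will be offered the opportunity to join their local Sparky Samba group".
- Table 1, retention row: the percentage "of participants attending the primary 12-week endpoint assessment (100*(number attending/number consented". Retention covers both arms and has the same denominator as adherence.
- Analysis: overall green requires every Table 1 criterion to be green, and the trial is "red (do not progress to full RCT unless major changes are implemented) if at least one criterion is in the red zone". This section restates adherence with the eight-session definition and points back to Table 1. It does not limit the denominator to one arm.

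**The concern.** The numerator can come only from participants allocated to Sparky Samba, while the denominator counts both arms. The bands, with green at 80% and red below 50%, make sense for a proportion of the intervention arm. Applied to a proportion of all who consented, they put green out of reach and place the red/amber boundary almost exactly at the highest value attainable.

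Adherence is one of six criteria, and the overall verdict follows the worst of them. Applied as printed, the formula would very probably turn the primary outcome red for a reason unrelated to whether people attended. Changing the denominator after the data are in, and so moving the verdict from red to amber or green, would look post hoc even if done in good faith.

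**Working it through.** **Inputs.** 60 participants, allocated 1:1, so about 30 per arm (Trial design and setting; Randomisation). Adherence = 100 × adherent / consented; red <50%, green ≥80% (Table 1). Controls have no access before follow-up (Activities as usual).

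**1. The plan's own precision figure.** The worst case is a proportion of 0.5. The Wald half-width is 1.96 × √(0.25/n).

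- n = 60: 12.65 points (Wilson 12.26, Clopper-Pearson 13.19). The stated 13 points is reproduced.
- n = 30: 17.9 points (Wilson 16.8, Clopper-Pearson 18.7). It is not reproduced.

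So the precision statement also treats adherence as a proportion of all 60.

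**2. Ceiling of the criterion** = number in the intervention arm / number consented.

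| Intervention arm | Consented | Maximum |
|---|---|---|
| 29 | 60 | 48.3% |
| 30 | 60 | 50.0% |
| 31 | 60 | 51.7% |
| 32 | 60 | 53.3% |
| 30 | 62 | 48.4% |
| 30 | 65 | 46.2% |

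The last two rows illustrate people who consent but are never randomised. Green needs 0.80 × 60 = 48 adherent participants, when about 30 can qualify.

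**3. What good adherence looks like under the formula.** True adherence of 80%, 90% and 95% in an arm of 30 appears as 40%, 45% and 47.5% of 60, all red. In particular 24/30 = 80% becomes 24/60 = 40%.

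**4. Probability of red.** Amber needs at least 30 adherent out of 60 consented. With exactly 30 in the arm, all must adhere, so P(red) = 1 − p³⁰ if participants adhere independently with probability p. With 31 or 32 in the arm it is the binomial probability of fewer than 30.

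| True adherence | Arm of 30 | Arm of 31 | Arm of 32 |
|---|---|---|---|
| 80% | 0.999 | 0.991 | 0.968 |
| 90% | 0.958 | 0.830 | 0.633 |
| 95% | 0.785 | 0.463 | 0.214 |

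With 29 in the arm, red is certain. The article does not give block sizes or the number of strata. Simulating stratified permuted blocks with assumed sizes 2, 4 and 6 and either two or five strata, the arm was usually 28–32. P(red) averaged over that imbalance was about 0.99 or higher at 80%, 0.92–0.93 at 90% and 0.74–0.76 at 95%. P(green) is zero throughout.

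**5. With the intervention arm (30) as denominator.** Green is ≥24/30 and red is <15/30.

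| True adherence | P(green) |
|---|---|
| 80% | 0.61 |
| 85% | 0.85 |
| 90% | 0.97 |
| 95% | 0.999 |

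P(red) is about 0.00005 at 80% and about 0.006 at 70%. The thresholds then discriminate as they appear meant to.

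**The case against.** The best defence is that this is a slip in one table cell. The thresholds fit only the intervention arm, the Intervention section uses the word participants for those attending sessions, and the analysis plan, which is not shown, might state the right denominator. That is a fair guess at intent, but it does not remove the error. The formula is printed in full, nothing in the article limits it to one arm, and the 13-point precision statement fits the literal reading.

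Other objections limit how far the point can be taken, and they stand. A reader might infer any of the following:

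- *The criterion can never exceed 50%, and a single non-adherent participant makes the trial red.* Both need exactly equal arms. Permuted blocks can leave 31 in the intervention arm, and one non-adherent participant then gives 30/60 = 50%, which is amber.
- *The denominator is at least 60.* Table 1 itself provides for 45–60 recruited as green and 25–44 as amber, so it may be smaller. The ceiling stays near 50% either way.
- *Red is almost certain however good adherence is.* That fits true adherence up to about 90%. At 95% red is likely (about 0.74–0.79), not almost certain.
- *Red ends the programme.* The rule allows progression if major changes are made.

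The probabilities also assume independent attendance. Participants share three community groups and may miss sessions together, so the decimals are illustrative. The ceiling does not depend on that assumption.

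**Conclusion.** The adherence criterion is wrong as written. Its ceiling is about 50%, so the adherence row cannot be green and the trial cannot be green overall. This follows from 1:1 allocation and the all-consented denominator alone, and no plausible arm imbalance brings 48 of 60 within reach.

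Red is very likely at true adherence up to about 90% (roughly 0.92 or higher, with or without allowance for imbalance) and likely at 95%. These probabilities rest on 60 consented, about 30 allocated to Sparky Samba, independent attendance and, for the imbalance figures, assumed block sizes and strata. They describe what happens if the printed formula is applied literally. The documents do not show that the analysts will in fact do so. Because the error sits in the decision rule for the primary outcome and is nearly free to correct, it should be corrected before the criteria are assessed.

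**What to change.** - In the adherence row of Table 1 and in the Analysis text, set the denominator to participants randomised to the Sparky Samba arm: 100 × (number attending at least eight sessions / number randomised to Sparky Samba). Keep the red, amber and green thresholds.
- As a proposal, since the article does not say, count participants in that arm who never start or who withdraw as non-adherent.
- In Trial design and setting, give adherence its own precision: with about 30 participants the worst-case 95% half-width is about 18 points. The 13-point statement does not hold for a rate estimated in one arm.
- Carry the same definition into the statistical analysis plan.

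The cost is a few lines of text and a less favourable stated precision for adherence. No new data are needed, because attendance is already collected by weekly self-report and group registers.

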### Safety monitoring

Adverse events will be recorded at the 12-week follow-up assessment, and participants will be encouraged to self-report any serious adverse events during the intervention delivery period to their recruiting site for inward reporting. Falls are a known facet of living with PD and may be regarded by some participants as an everyday occurrence. However, we will attempt to record all incidences of falls regardless of severity.

### Process evaluation

To understand barriers and facilitators to intervention delivery as well as the contextual mechanisms for potential effectiveness, we will embed a process evaluation in line with Medical Research Council guidance for the evaluation of complex interventions.^25^ The process evaluation will use both qualitative and quantitative data. All intervention delivery staff will be asked to take part in semi-structured interviews, conducted by a trained qualitative researcher. Additionally, intervention delivery staff will be asked to contribute reflections on intervention delivery, including specific items pertaining to fidelity of intervention delivery, in a structured questionnaire. This will be used to assess fidelity and understand the key mechanisms of change. Trial participants and their support partners (if willing) will be asked to complete a structured questionnaire that focuses on their views of the trial and of the intervention using a mix of Likert-style questions and free text responses. Participants can choose to type the free text responses or respond to these in a semi-structured interview. We will also attempt to contact any participants who drop out of the intervention to ascertain reasons for discontinuing.

### Data collection and management

Study data will be collected and managed using REDCap electronic data capture tools hosted at Cardiff University.^19
20^ REDCap is a secure, web-based software platform designed to support data capture for research studies, providing (1) an intuitive interface for validated data capture, (2) audit trails for tracking data manipulation and export procedures, (3) automated export procedures for seamless data downloads to common statistical packages and (4) procedures for data integration and interoperability with external sources.

All trial data recorded in REDCap features in-built data validations and mandatory completion of specific variables to promote quality control and data completion. Outcome data will be collected through a combination of patient-reported outcome measures (PROMs) completed directly within the database and in-person assessments conducted by research staff at the site (table 3). Following the provision of informed consent and confirmation of a baseline appointment from trial staff at the recruitment site, participants will be emailed a link to complete the PROMs ahead of their baseline assessment. If a participant chooses, they can complete the PROMs on paper copies at their baseline appointment. If a participant attends their baseline or follow-up appointment without having previously completed the PROMs in REDCap, they will be supported to do so either face to face at the appointment or by telephone by a member of the trial team.

Intervention adherence data will be collected directly from participants via REDCap. Participants will be emailed a brief attendance checklist weekly for up to a period of 14 weeks from the point of randomisation. Samba group leaders and group coordinators (local volunteers) will be asked to provide data on attendance on a pre-populated register provided to them by the central trial team.

Similarly, process evaluation questionnaires will be distributed through REDCap for remote completion. Process evaluation interviews will be conducted remotely using secure video conferencing software. Interviews will be audio recorded for verbatim transcription. Audio recordings will be deleted once transcripts have been cleaned, de-identified and incongruences verified. De-identified transcripts will be stored on a restricted access computer drive at Cardiff University.

All data management processes for the trial are contained in the Sparky Samba Data Management Plan.

### Data monitoring

A monitoring plan has been developed according to the trial risk assessment. Given the low-risk nature of the study, no routine on-site monitoring is planned. Consent and participant eligibility provided via REDCap is monitored following notification of participant registration. Outcome data entered into REDCap is monitored for accuracy and spurious entries on a monthly basis and any queries raised with sites via e-mail. All data queries, participant status metrics (recruitment, withdrawal, data completeness and intervention adherence), safety events and protocol non-compliances are monitored monthly at TMG meetings.

### Analysis

Key demographic data will be summarised using descriptive statistics. For feasibility outcomes, recruitment will be assessed as the percentage of people approached who provide consent to participate in the trial; retention as the percentage of participants recruited who attend the 12-week follow-up assessment (primary endpoint); adherence as the percentage of participants adherent to the intervention (where intervention adherence is defined as attending ≥8 of 12 sessions) and data completeness as the percentage of participants completing ≥90% of baseline and follow-up measures, respectively (table 1). Feasibility criteria will be assessed according to a traffic light system with green (proceed to full effectiveness RCT) if all criteria listed in table 1 are in the green zone; amber (requiring adjustment before proceeding to full RCT) if all criteria are either in the amber or green zone; and red (do not progress to full RCT unless major changes are implemented) if at least one criterion is in the red zone. For secondary outcome measures, we will calculate descriptive summaries by arm, such as mean and standard deviation (or median and IQR, in case of a distinctly non-normal distribution) and 95% CIs of participants’ changes from baseline to 12-week follow-up. This will provide estimates of effect size and variability of drumming-induced changes for use in power calculations for a future large-scale RCT. No sub-group, sensitivity or interim analyses will be conducted. Reporting of results will follow the Consolidated Standards of Reporting Trials (CONSORT) guideline extension for pilot and feasibility studies.^26^ The statistical analysis plan will be available via ISRCTN (*ISRCTN11861663*).

Following each interview, notes will be re-read and audio recordings replayed to identify initial ideas or areas of interest. Interviews will be transcribed verbatim, and transcripts along with free text responses to the questionnaires will be analysed thematically.^27^ Analysis will be an iterative and ongoing process throughout data collection. After familiarisation with the data, preliminary codes will be generated to label data relevant to the research objectives. Coded data will then be collated to generate themes, with summaries produced for each theme to map intervention components and activities, contributing to the development of a logic model. We will visually arrange the data to build an overall picture of the whole data set. The next stage will involve the research team using the summaries to examine the quality and boundaries of themes identified. From this, we will finalise a thematic map, refining the specifics of each theme to capture key concepts and produce analytical commentary and interpretation of the data set as a whole and connect it with the original research objectives. The qualitative software package, NVivo (2015), will be used to manage the data. The data and analysis will be reviewed by members of the research team and checked for accuracy with those taking part in Sparky Samba.

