**Analysis:**

Feasibility outcomes will be assessed according to pre-defined criteria. For secondary outcomes, means and standard deviations (or medians and IQRs) will be calculated by arm, alongside 95% CIs for change from baseline to 12-week follow-up. Qualitative data will be subject to thematic analysis using NVivo software.

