Sparky Samba has achieved support from the PD community (both PwP and the UK’s leading PD charity, Parkinson’s UK (PUK)) and arts-based funders but it warrants further investigation for its potential health benefits. The Sparky Samba intervention will be compared with an activities as usual control group. Our PD community members have indicated many people take part in other PD-specific groups, such as seated bowling or choirs, which have a similar duration to Sparky Samba sessions but are sporadic in their geographic availability. By using an activities-as-usual control, we aim to differentiate between the community and social aspects of standard social activities versus the specifics of the Sparky Samba intervention and potential benefits of rhythmic-based activities.

The aim of this study is to evaluate the feasibility of Sparky Samba in a small-scale randomised controlled trial (RCT) as a next step towards a full effectiveness evaluation of Sparky Samba as a health intervention for PwP.

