### Objectives

The primary objective of the Sparky Samba trial is to determine the feasibility of conducting a full-scale effectiveness RCT of the Sparky Samba intervention. The secondary objective is to explore the effect of Sparky Samba on functional and well-being measures, compared with activities as usual, in PwP.

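### The secondary objective compares the arms, but the stated analysis gives only change within each arm and presents it as the drumming effect for powering the next trial

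*Protocol article*

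**What the plan says.** The Objectives section of the protocol article states: "The secondary objective is to explore the effect of Sparky Samba on functional and well-being measures, compared with activities as usual, in PwP". The Introduction gives the control arm a contrasting role: "we aim to differentiate between the community and social aspects of standard social activities versus the specifics of the Sparky Samba intervention". Under Trial design and setting: "We will recruit 60 PwP to be randomised 1:1 to the intervention or activities as usual for a period of 12 weeks".

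The Analysis section then specifies: "For secondary outcome measures, we will calculate descriptive summaries by arm, such as mean and standard deviation", with median and IQR for clearly non-normal data, and "95% CIs of participants’ changes from baseline to 12-week follow-up". The abstract matches it: means and SDs, or medians and IQRs, "will be calculated by arm, alongside 95% CIs for change from baseline to 12-week follow-up". Neither place names a difference between arms or an interval for one.

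The next sentence of the Analysis section says what this output is for: "This will provide estimates of effect size and variability of drumming-induced changes for use in power calculations for a future large-scale RCT".

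**The concern.** The objective asks what Sparky Samba does relative to usual activities. The quantity given a confidence interval is how much each arm moved from its own baseline. These are different estimands, and the article describes the second as if it were the first.

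Several features of the design make the distinction matter:

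- The trial is not blinded, apart from the video rating of UPDRS Part III. Six of the nine measures in Table 2 are self-reported (FoG, DREFAQ, PASE, PDQ-8, OxPAQ, Lorig), so expectation can move them.
- Other treatment is unrestricted during the 12 weeks (Activities as usual section), and Table 3 collects medications at baseline only.
- Usual activities may include walking or the gym, so controls may change too.

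The sentence also names a consequence, the power calculation for a full RCT. An effect size that is really a change within one arm would mis-size that trial whenever the control arm moves.

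**Working it through.** **The plan's own precision figure.** The article gives one, for proportions with N = 60: at most ±13 percentage points. Wald half-width at 50%: 1.96 × √(0.25/60) = 0.1265, or 12.65 points. It reproduces, but it concerns the feasibility rates. No precision is stated for the secondary outcomes.

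**Inputs.** 30 per arm (60 randomised 1:1). 27 per arm is 90% of 30, the green retention threshold in Table 1. The article gives no SD, so results are in units of the SD of change, taken as equal in the two arms.

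**What is planned and what the objective needs.**

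| Quantity | Formula (half-width of 95% CI) | 30 per arm | 27 per arm |
|---|---|---|---|
| Change within one arm | t(n−1) × √(1/n) | 0.373 | 0.396 |
| Difference in change between arms | t(2n−2) × √(2/n) | 0.517 | 0.546 |

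At 30 per arm the interval for the difference is 0.517/0.373, about 1.38 times as wide as the within-arm interval. The planned intervals therefore look tighter than the evidence on the comparison.

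**Is the SD usable?** The 95% limits for a pooled SD are the estimate times √(df/χ²). With df = 52 the multipliers are 0.84 and 1.24; with df = 58 they are 0.85 and 1.22. That is adequate for planning. An observed effect of 0.4 SD, by contrast, would be compatible with about −0.1 to +0.9 SD (0.4 ± 0.52 to 0.55).

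**What baseline adjustment adds.** If baseline and follow-up variances are equal, the variance of the adjusted difference relative to the change-score difference is (1 + r)/2. For an assumed correlation r of 0.5 this is 0.75, and for 0.8 it is 0.90. The half-widths become 0.517 × √0.75 = 0.45 (30 per arm) to 0.546 × √0.90 = 0.52 (27 per arm), ignoring the few degrees of freedom used. The interval stays near ±0.5 SD of change.

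**When within-arm change equals the effect.** Intervention-arm change = effect + whatever would have happened anyway. The second term is zero only if controls do not change. For illustration, with assumed values: two-sided 5%, 90% power, SD of change 1, intervention-arm change 0.5. Then n per arm = 2 × (1.960 + 1.282)²/d². Using d = 0.5 gives 85.

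| Control change, same direction | True difference d | n per arm needed | Power with 85 per arm |
|---|---|---|---|
| 0 | 0.5 | 85 | 90% |
| 0.1 | 0.4 | 132 | 74% |
| 0.2 | 0.3 | 234 | 50% |
| 0.3 | 0.2 | 526 | 26% |

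If controls instead moved 0.2 SD the other way, d = 0.7 and 43 per arm would do (21.01/0.49 = 42.9), so the error can run in either direction. These figures show how sensitive the result is to the choice of quantity. They do not predict what the sponsor will do.

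**The case against.** The strongest reply is that this is a feasibility trial, expressly not powered for tests on clinical outcomes, and that descriptive summaries are the right tool. That stands as far as tests go, and none is asked for here. It does not exclude an estimate with an interval, which the article already plans, though for a different quantity.

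Second, the statistical analysis plan and full protocol are said to be available through the registry and were not seen. A reader might infer that no between-arm comparison is planned at all. The article does not establish that; it shows only that none is named where the analysis is described. What remains is the article's positive statement about what the named summaries deliver, and further detail elsewhere would not make that statement correct.

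Third, a reader might infer that randomisation goes unused or that the objective cannot be addressed. That is too strong. Both randomised arms are summarised, and for outcomes reported as means the difference and its interval can be recovered. At 30 per arm each standard error is 0.373/2.045 = 0.183; the standard error of the difference is 0.183 × √2 = 0.258; and 2.002 × 0.258 = 0.517. But the reader has to do this, it is unadjusted, and it is not available where only medians and IQRs are given.

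Fourth, it is tempting to read the sentence as a plan to power on the intervention arm alone, or to judge the arms by looking at two intervals side by side. The article proposes neither, and effect size could be meant as a between-arm quantity. Choosing the next trial's target from a minimally important difference is likewise advice for that trial, not an error in this one.

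**Conclusion.** The concern holds in a limited form. The objective is comparative, the analysis as stated names no comparison, and by-arm changes are wrongly described as yielding the size of drumming-induced change. They estimate the intervention effect only on the assumption that controls do not change, which an unblinded trial with unrestricted treatment gives no reason to make.

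The causal label would be too strong even for the between-arm difference. Under Strengths and limitations the article concedes that the comparator does not fully control for social interaction, and expectation that differs between arms would remain in the self-reported measures.

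The variability part of the sentence is sound: by-arm SDs of change are valid planning inputs. The effect part is not, and even the correct estimate would be known only to about ±0.5 SD of change. That figure assumes 27 to 30 analysed per arm and equal SDs. The adjusted version also assumes a correlation of 0.5 to 0.8, which the article does not give.

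This should be corrected, but it does not threaten the trial. Progression rests on the Table 1 criteria alone, and no secondary-outcome estimate enters them.

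**What to change.** 1. For each secondary outcome, add an exploratory between-arm difference at 12 weeks with a 95% CI and no p-value. Take it from a linear model of the 12-week value on arm, baseline value and the Hoehn and Yahr randomisation stratum.
2. Report the residual SD and the correlation between baseline and 12 weeks, alongside the by-arm SDs of change already planned.
3. Reword the sentence on the future power calculation and delete *drumming-induced*. For example: *The by-arm changes inform the variability to be assumed in a future power calculation; the between-arm difference is an imprecise, exploratory estimate of the effect of Sparky Samba compared with activities as usual.*
4. Make the abstract consistent with this.

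The cost is one extra model per outcome and a few lines of text. Table 3 already schedules the baseline values, the 12-week values and Hoehn and Yahr stage, so no new data or participants are needed. The drawback is that the intervals will be wide and must be labelled exploratory so that they are not read as evidence for or against effectiveness.
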